### Aims

2.2

The primary aim of the study aims to evaluate the hypothesis that the Team Care model will result in greater % weight loss across 18 months compared to the Local Care + arm. Secondary aims will examine whether Team Care leads to:1.Higher rates of achieving ≥5 % and ≥10 % weight loss at 6, 12, and 18 months.2.Improved outcomes in weight (kg), diet quality, physical activity, and quality of life across 6, 12, and 18 months.

Tertiary aims will compare the effects of the two treatments on mental health, pain, sleep quality, and medical treatment process outcomes (participant activation, participant-provider communication, discussion and prescription of weight loss medications, and discussion and referral for bariatric surgery) across the study. We will also evaluate the uptake of pharmacotherapy and bariatric surgery and their potential impact on the between-arm difference in % weight loss. Exploratory aims will evaluate reach, adoption, implementation, and maintenance of the intervention according to the RE-AIM evaluation framework [23]; and to investigate rural sociocultural and spatial predictors of treatment effects.

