### Cluster randomization

2.4

Primary care practices will be randomly allocated in equal proportions (1:1) to each of the two study arms (Team Care, Local Care) in pairs after the target number of participants at the sites have been screened eligible and eligible participants have completed their initial baseline surveys. Eight practices are expected to enroll into each arm. Participants remain blinded to randomization until fully enrolled in the study. Practice staff will be notified during final participant enrollment steps to allow for sufficient lead time for practice staff to schedule the first quarterly clinic visits approximate in time to the baseline weight measurement.

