#### Exploratory measures

2.10.5

The RE-AIM evaluation framework [23] is used to explore the potential population-level impact and generalizability of the intervention in real-world clinical settings. To Measure reach, patient participation rates will be calculated using the registry lists as the denominator and representativeness of enrolled participants versus non-participants are compared based on baseline BMI, age, rurality, and sex. Adoption, implementation, and maintenance at the clinic level will be explored through mixed methods including study-specific surveys and focus groups with participating PCPs. To explore the relative importance of place and context for impacting outcomes, multiple participant-level and spatial-level measures will be collected. Participant-level contextual measures will be collected at baseline. Spatial level measures will be captured from available public data based on participants’ home addresses and include social disadvantage indicators from the American Community Survey [61], food dessert indicators from the USDA Food Access Research Atlas [62], and county-level prevalence of obesity, physical inactivity based on County Health Rankings [63].

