#### Sample size

2.11.1

As little as 3–5 % weight loss is clinically meaningful [64]. In RE-POWER, a clinic group-based intervention showed 4.3 % loss at 24 months, and we expect a larger mean effect from the additional medical management component. To determine sample size, we set the type I error at 0.05, intraclass correlation coefficient at 0.02 as was observed in RE-POWER, and 35 participants per clinic. With 16 clinics, the trial will have 85 % power to detect a net between-group treatment effect of 3 % (SD = 8).

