#### Secondary and exploratory aims

2.11.4

Each secondary outcome at 18 months will be compared across arms using separate hierarchical linear mixed model in a similar strategy as the primary aim, except for the proportion achieving clinical cut points of 5 % and 10 % weight loss. These will be compared across arms usings generalized linear mixed models.

To evaluate the impact of pharmacotherapy and bariatric surgery on the between-arm difference in % weight loss, we will add receipt of pharmacotherapy and bariatric surgery to the primary aim to estimate the influence of each on % weight loss beyond other aspects of the intervention. We will use generalized linear mixed models to estimate the proportion who begin pharmacotherapy or undergo bariatric surgery, adjusting for baseline covariates (age, sex, race, education, BMI, insurance, co-morbid conditions), and then multiply the proportion by the effect on % weight loss to calculate impact for each arm, using bootstrapping to derive confidence intervals. We will also conduct a sensitivity analysis on the primary analysis, excluding participants who receive one or both.

Mental health, pain, sleep quality and other medical treatment process outcomes will be compared across treatment arms at 6 and 18 months using separate mixed models in a similar strategy as the primary and secondary aims. Each RE-AIM measure will be compared across treatment arms using descriptive statistics.

To explore the associations between participant-level and tract/county-level contextual measures and % weight loss, we will use hierarchical linear models including variables with the strongest bivariate associations (p < 0.10).

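### The exploratory aim asks what predicts the treatment effect, but the one stated analysis, screened at p < 0.10, would identify predictors of weight loss; the two need reconciling

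*Protocol article*

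**What the plan says.** Three places in the protocol article describe this piece of work, and they do not name the same target.

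- Section 2.2 (Aims) lists, among the exploratory aims, "to investigate rural sociocultural and spatial predictors of treatment effects".
- Section 2.10.5 (Exploratory measures) gives a looser purpose: "To explore the relative importance of place and context for impacting outcomes, multiple participant-level and spatial-level measures will be collected".
- Section 2.11.4 (Secondary and exploratory aims) gives the analysis. Its target is "To explore the associations between participant-level and tract/county-level contextual measures and % weight loss", and its method is: "we will use hierarchical linear models including variables with the strongest bivariate associations", with p < 0.10 as the threshold.

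The sentence in 2.11.4 does not say how study arm enters the screen or the final model. Section 2.11.5 adds only sensitivity analyses that adjust for baseline variables found to differ between arms.

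**The concern.** A variable that predicts weight loss and a variable that predicts the effect of Team Care over Local Care are different things. The first is a slope on the outcome. The second is a difference in slopes between arms, that is, an arm-by-variable interaction. The aim in 2.2, read literally, asks for the second; the analysis in 2.11.4 delivers the first.

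The selection rule adds to the mismatch. A bivariate screen against weight loss ranks variables by their average association with the outcome. It keeps strong prognostic factors whether or not they modify the effect, and it can drop a modifier whose slopes offset each other across arms.

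At stake is the interpretation. Set beside the aim in 2.2, a list of variables that survived the screen could be reported as showing for whom, or in which rural settings, Team Care works better. The analysis as described would not support that statement.

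**Working it through.** **Inputs.** From section 2.11.1: "we set the type I error at 0.05, intraclass correlation coefficient at 0.02 as was observed in RE-POWER, and 35 participants per clinic"; also 16 clinics, a between-arm difference of 3 points, SD 8 and 85% power. From 2.4: "Eight practices are expected to enroll into each arm". From 2.11.2: at least 85% retained at 18 months. A two-sided test is assumed, since sidedness is not stated.

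**The plan's own figure.** With 85% retention, clinic size is 35 × 0.85 = 29.75. The design effect is 1 + 28.75 × 0.02 = 1.575. Effective size per arm is 8 × 29.75 / 1.575 = 151.1, and the standard error of the difference is 8 × √(2/151.1) = 0.92. A noncentral t with 14 df gives 85.8% power, which reproduces the stated 85%. This figure is not in dispute; it confirms that the inputs are read correctly.

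**What the screen measures and what the aim needs.** Let the slope be b_T in Team Care and b_L in Local Care. With equal arms and the screen run on both arms together (an assumption, as 2.11.4 does not say), the screened slope is (b_T + b_L)/2. The effect modification is b_T − b_L. The slopes below are assumed for illustration. Simulation: 4,000 runs, 16 clinics of 35 with no dropout, total SD 8, ICC 0.02, arm difference 3, balanced binary participant-level factor.

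| b_T, b_L | Screened slope | Modification | Passes p < 0.10 screen | Interaction test at 0.05 rejects |
|---|---|---|---|---|
| +2, −2 | 0 | 4 | 9.8% | 83.5% |
| +1.5, −1.5 | 0 | 3 | 9.7% | 59% |
| 3, 0 | 1.5 | 3 | 69% | 60% |
| 3, 3 | 3 | 0 | 99.7% | 4.2% |

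A pure crossover modifier passes at about the 10% chance rate. A factor that modifies nothing passes almost always. A factor acting in one arm only often passes, but a model of its association with weight loss still returns a single slope and not the difference of 3.

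**Precision of an interaction.** Retained sample: 560 × 0.85 = 476, or 119 in each of the four arm-by-factor cells.

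- Balanced participant-level factor, clustering ignored: SE = 8 × √(4/119) = 1.47 points. Removing the clinic component of variance gives 8 × √0.98 × √(16/476) = 1.45. The interaction detectable with 80% power is then 1.45 × (1.96 + 0.84) ≈ 4.1 points, or about 3.8 with all 560. Power for an interaction of 3 points is about 54%.
- Limiting case of a factor constant within clinic, 4 clinics per cell: SE = 8 × √(4 × 1.575/119) = 1.84 points. With 12 df, the interaction detectable with 80% power is about 5.6 points. Tract and county factors would tend towards this case to the extent that they vary little within a clinic.

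**The case against.** The strongest reply is that 2.2 contains one loose phrase. Section 2.10.5, which introduces these measures, speaks of context affecting outcomes, and the analysis in 2.11.4 fits that purpose. Section 2.11.1 also uses the word effect for the mean loss under one intervention, and marks the contrast separately as net and between groups. So the aim could mean weight loss achieved under treatment. This reading is possible and cannot be ruled out. It does not remove the point: the three sections still need to agree, and on this reading the repair is to reword the aim.

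A reader might infer something stronger: that the plan pools the arms, excludes any interaction and so cannot answer its aim. The document does not support that. Section 2.11.4 is one condensed sentence that is silent on arm; it does not say that arm is left out. Model terms are commonly left to the full protocol or analysis plan, which is not shown. What the article does fix is the analysis target (association with weight loss) and the selection rule, and those are what can be criticised.

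Three further limits stand. Zero average association needs equal and opposite slopes, and nothing in the document suggests such a crossover. The general complaint that p-value screening overstates the surviving coefficients is separate and unquantified here, and the article claims no confirmatory status for these models. Nor does the trial's assessment of reach depend on this: 2.10.5 defines reach by participation rates and representativeness.

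Finally, the interaction estimates would be imprecise; the detectable interactions above exceed the 3-point difference the whole trial is sized for. That limits what the remedy can deliver, but it does not make an association with weight loss into evidence of effect modification.

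**Conclusion.** The point holds as a mismatch between aim and stated analysis. Read literally, 2.2 asks about modification of the between-arm effect; 2.11.4, followed as written, yields predictors of percent weight loss, chosen by a rule that favours prognostic factors and can discard modifiers. The percentages rest on assumed slopes, a balanced binary participant-level factor, full retention and a screen across both arms. They show the direction of the problem, not the expected loss in this trial. It would be going too far to say that the trial is unable to study effect modification, because the article does not say how arm enters and the full plan may do so.

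The consequence is confined to an exploratory aim. The primary comparison and the secondary and tertiary comparisons between arms are untouched.

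**What to change.** Decide which question is meant and make 2.2, 2.10.5 and 2.11.4 say the same thing.

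- If effect modification is meant: fix a short list of contextual factors before analysis. Add each factor and its interaction with arm to the primary mixed model, without the p < 0.10 screen. Report arm-specific slopes and interaction estimates with confidence intervals for every factor on the list, labelled exploratory. Associations with weight loss can stay as a separate descriptive result.
- If predictors of weight loss are meant: reword the aim in 2.2 accordingly, and do not interpret the results as showing for whom or where Team Care works better.

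Either route needs no new data. The first costs some wording and a few extra models, and its intervals will be wide, more so for tract and county factors with only 16 clinics. The second costs wording alone.

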#### Potential confounders

2.11.5

For all statistical models, sensitivity analyses will be performed using the models above but also adjusting for potential confounders among the baseline variables identified as varying across arms based on their standardized differences.

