#### Medical treatment process outcomes

2.10.4

The Patient Activation Measure (PAM-13) [52] will evaluate the degree to which the intervention, including the lifestyle coach's involvement in team visits, improves patient engagement, i.e., ability to be involved in treatment, collaborate with providers, and engage in health-promoting behaviors. Team-based care for activating chronic disease self-management and exercise has been shown to improve PAM-13 scores, and a difference of ≥5 points is considered meaningful [53,54]. Treatment process measures related to medical management of obesity is captured using a modified version of the Patient Assessment of Chronic Illness Care (PACIC-5A) measure for obesity treatment in primary care [55]. Participant's past use, perceived safety, and perceived effectiveness of various weight loss methods will be assessed. Survey items are derived from a previous survey that measured perceived safety and efficacy of weight loss methods in patients with obesity [56].

Participants will also assess the helpfulness of their PCP in their weight management using a single item measure that has been associated with greater weight loss in prior primary care-based trials [17]. All medications will be collected at baseline using a structured interview tool where patients gather and report all medications, a method that has resulted in 95 % accuracy [57]. At follow up timepoints, patients will self-report medications for weight loss and/or diabetes via survey, allowing us to identify prescriptions for new weight loss medications. Satisfaction with clinic services and overall satisfaction is measured by items derived from the Integrated Care Performance measure recommendations from the Center for Health Care Strategies [58]. Additionally, counseling satisfaction and group counseling cohesion is measured for patients in the team care arm using items derived from measures previously developed for behavioral weight loss interventions [59,60].

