#### Statistical analysis for primary aim

2.11.3

Percent weight loss at 18 months will be compared between the treatments. Hierarchical linear mixed models will be used to examine the group differences, accounting for the correlation between participants from the same clinic and for the correlation of measures from the same participants.

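### The article names no baseline covariate for the primary model, and its sensitivity analyses choose covariates by observed imbalance between arms; a short prognostic set should be fixed in advance

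*Protocol article*

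**What the plan says.** For the primary aim (Section 2.11.3) the article gives the model class and the correlation structure: "Hierarchical linear mixed models will be used to examine the group differences, accounting for the correlation between participants from the same clinic", and also for repeated measures on the same participant. It lists no baseline covariate and does not say that there are none.

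Section 2.11.5 covers all statistical models. Sensitivity analyses rerun the models already described, this time "adjusting for potential confounders among the baseline variables identified as varying across arms based on their standardized differences". It gives neither a cut-off nor a list of candidate variables.

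A fixed covariate list does appear in Section 2.11.4, but only in the model for starting pharmacotherapy or having bariatric surgery: "adjusting for baseline covariates (age, sex, race, education, BMI, insurance, co-morbid conditions". In Section 2.10.4, "All medications will be collected at baseline using a structured interview tool". Current use of weight-loss medication is not among the exclusions in Section 2.5.

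**The concern.** A covariate improves a randomised comparison to the extent that it predicts the outcome. Observed imbalance between arms does not measure that. Under the stated rule, a strong predictor of weight loss that happens to balance stays out, and a variable with no bearing on weight loss can come in because it happens to differ. The content of the adjusted model cannot be known until baseline data have been compared by arm.

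The design makes such imbalance likely. Only 16 units are randomised, so chance differences are larger than 560 participants would suggest. In addition, Section 2.7 places consent and the baseline weight visit after the clinic's randomisation, and Section 2.4 has practice staff told of the allocation during the final enrolment steps. A difference between arms may therefore reflect who completed enrolment as well as chance. A reader of an adjusted result chosen after the fact could not easily tell which was being corrected.

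At stake are some precision in the primary comparison and the clarity of the adjusted one. Baseline use of weight-affecting medication, for instance, is recorded but is not assured a place in any model of weight loss that the article describes.

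**Working it through.** **Inputs from the protocol article.** Section 2.11.1 states the target: "With 16 clinics, the trial will have 85 % power to detect a net between-group treatment effect of 3 % (SD = 8". The other inputs there are a type I error of 0.05 (taken as two-sided), an ICC of 0.02 carried over from the group's previous trial, and clinics of 35. Section 2.4: "Primary care practices will be randomly allocated in equal proportions (1:1) to each of the two study arms", that is 8 clinics and 8 × 35 = 280 participants per arm. Section 2.11.2: retention of at least 85%, with a goal of 90%.

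**Assumptions, not in the article.** Cut-offs of 0.10 and 0.25 for a standardised difference; covariate intraclass correlation (ICC) from 0 to 0.10; share of outcome variance explained by covariates (R²) from 0.05 to 0.15, with 0.10 and 0.20 used in a simulation.

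**1. The plan's own power.** With m participants per clinic,

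SE = √{ (2/8) × [ICC × SD² + (1 − ICC) × SD² / m] },

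and power comes from a noncentral t with 16 − 2 = 14 degrees of freedom.

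- m = 35: SE = 0.876, power 88.9%.
- m = 35 × 0.90 = 31.5: SE = 0.904, power 86.9%.
- m = 35 × 0.85 = 29.75: SE = √{0.25 × [1.28 + 62.72/29.75]} = 0.920, power 85.8%.

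The stated 85% is reproduced to within a point with 85% retention and no covariate gain. The article does not say that retention was built in.

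**2. How often a truly balanced variable is flagged.** SE of a standardised difference = √{ (2/280) × (1 + 34 × ICC) }.

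| Covariate ICC | SE | Chance above 0.10 | Chance above 0.25 |
|---|---|---|---|
| 0 | 0.085 | 24% | 0.3% |
| 0.02 | 0.110 | 36% | 2% |
| 0.05 | 0.139 | 47% | 7% |
| 0.10 | 0.177 | 57% | 16% |

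For illustration, take seven independent candidates, the length of the list in Section 2.11.4, each with ICC 0.02. At a cut-off of 0.10, 7 × 0.361 = 2.5 are flagged on average, and at least one in 1 − (1 − 0.361)⁷ = 96% of trials. At 0.25, at least one is flagged in 15%. The result depends heavily on a cut-off that the article does not give.

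**3. What fixed covariates would add.** Multiply the within-clinic variance by (1 − R²), and the between-clinic variance too if the covariates explain it. Keep m = 29.75 and 14 degrees of freedom.

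| R² | Power, both levels | Power, within clinic only |
|---|---|---|
| 0 | 85.8% | 85.8% |
| 0.05 | 87.5% | 86.8% |
| 0.10 | 89.1% | 87.9% |
| 0.15 | 90.7% | 88.9% |

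The gain runs from 86.8 − 85.8 = 1.0 point to 90.7 − 85.8 = 4.9 points.

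**4. Does the selection rule do harm?** This was simulated with 3,000 trials per setting, 35 per clinic with no dropout, the ICC treated as known, seven equally prognostic covariates with ICC 0.02, and a cut-off of 0.10. Imbalance arose by chance only.

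| | Unadjusted | Fixed set | Picked by imbalance |
|---|---|---|---|
| Null rejection, R² 0.20 | 4.6% | 4.9% | 3.7% |
| Power, R² 0.20 | 92.7% | 96.8% | 95.3% |
| Null rejection, R² 0.10 | 4.4% | 4.7% | 4.1% |
| Power, R² 0.10 | 92.9% | 94.9% | 94.0% |

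Mean error of the estimate was at most 0.03 percentage points throughout. Under the null with R² 0.20, the imbalance-picked analysis reported a mean standard error of 0.847 against an actual 0.792, so it is somewhat conservative. The simulation covers neither irrelevant candidates nor differential enrolment.

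**The case against.** **The article is condensed.** Section 2.11.3 is two sentences long, and a covariate list may stand in the full protocol or the analysis plan. A reader might infer that the primary model is declared to be unadjusted. The text does not say so. That it adjusts for nothing is an inference from naming no covariate and from the wording of Section 2.11.5, which adds adjustment to models already described; that wording would also fit a primary model with a fixed set. This objection stands. It does not remove the selection rule, which the article states outright and applies to every model.

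**Only sensitivity analyses are affected.** This also stands. A reader might infer that the primary result is data-driven, or that the rule inflates type I error. The first is contradicted by Section 2.11.5 itself, and the simulation shows no sign of the second.

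**The rule may contain two filters.** The wording could mean variables that are both imbalanced and plausible confounders. That softens the worry about irrelevant variables. Imbalance would still be a necessary condition, so prognostic variables that balance would still be left out.

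**Looking at imbalance has a purpose here.** Because enrolment finishes after clinic randomisation, a check that responds to observed imbalance is reasonable. This stands as a reason to keep such a check as a supplement. It is equally a reason to fix the main adjusted model beforehand.

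**The size rests on assumptions.** The cut-off, covariate ICC and R² are not in the article. With a cut-off of 0.25 and ICC 0.02, few variables would be flagged.

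**Conclusion.** The concern holds in a limited form. The article names no covariate for the primary model, implies that baseline variables enter only in sensitivity analyses, and selects them there by a criterion that does not measure prognostic value. With 16 clinics that criterion can respond largely to chance, and possibly to differential enrolment.

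The cost is modest: about 1 to 5 points of power if covariates explain an assumed 5% to 15% of variance, and an adjusted model whose content is unknown in advance. A reader might conclude that the trial is underpowered, but the stated 85% is met without any covariate, so this is a missed gain and not a sample-size error. The change is worth making because it is nearly free; the primary analysis is valid without it.

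**What to change.** - In Section 2.11.3, name a short prognostic set for the primary model, for example baseline weight or BMI, age, sex and baseline use of weight-affecting medication. All are already to be collected. If the full protocol or analysis plan already fixes such a set, state it here.
- Keep the unadjusted model as a sensitivity analysis.
- For other continuous outcomes, add the baseline value where one is measured. Table 4 shows none for clinical management of weight or for program satisfaction, and the 5% and 10% weight-loss cut points have no baseline value, so this cannot be a blanket rule.
- In Section 2.11.5, use standardised differences to describe balance. If adjustment triggered by imbalance is kept because enrolment follows randomisation, label it supplementary and state the candidate variables and the cut-off beforehand.

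The cost is a paragraph of wording, a few model degrees of freedom and one extra model run. No new data are needed.
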